## Abstract

**Background:**

Diabetic foot neuropathy (DFN) is one of the most important complications of diabetes mellitus; its early diagnosis and intervention can prevent foot ulcers and the need for amputation. Thermometry, measuring the temperature of the feet, is a promising emerging modality for diabetic foot ulcer prevention. However, patient compliance with at-home monitoring is concerning. Delivering messages to remind patients to perform thermometry and foot care might be helpful to guarantee regular foot monitoring. This trial was designed to compare the incidence of diabetic foot ulcers (DFUs) between participants who receive thermometry alone and those who receive thermometry as well as mHealth (SMS and voice messaging) over a year-long study period.

**Methods/design:**

This is an evaluator-blinded, randomized, 12-month trial. Individuals with a diagnosis of type 2 diabetes mellitus, aged between 18–80 years, having a present dorsalis pedis pulse in both feet, are in risk group 2 or 3 using the diabetic foot risk classification system (as specified by the International Working Group on the Diabetic Foot), have an operating cell phone or a caregiver with an operating cell phone, and have the ability to provide informed consent will be eligible to participate in the study. Recruitment will be performed in diabetes outpatient clinics at two Ministry of Health tertiary hospitals in Lima, Peru.

Interventions: participants in both groups will receive education about foot care at the beginning of the study and they will be provided with a thermometry device (TempStat™). TempStat™ is a tool that captures a thermal image of the feet, which, depending on the temperature of the feet, shows different colors. In this study, if a participant notes a single yellow image or variance between one foot and the contralateral foot, they will be prompted to notify a nurse to evaluate their activity within the previous 2 weeks and make appropriate recommendations. In addition to thermometry, participants in the intervention arm will receive an mHealth component in the form of SMS and voice messages as reminders to use the thermometry device, and instructions to promote foot care.

Outcomes: the primary outcome is foot ulceration, evaluated by a trained nurse, occurring at any point during the study.

**Discussion:**

This study has two principal contributions towards the prevention of DFU. First, the introduction of messages to promote self-management of diabetes foot care as well as using reminders as a strategy to improve adherence to daily home-based measurements. Secondly, the implementation of a thermometry-based strategy complemented by SMS and voice messages in an LMIC setting, with wider implications for scalability.

**Trial registration:**

This study is registered in ClinicalTrials.gov: Identifier NCT02373592.

**Electronic supplementary material:**

The online version of this article (doi:10.1186/s13063-016-1333-1) contains supplementary material, which is available to authorized users.

## Background

There are an estimated 392 million people worldwide living with type 2 diabetes mellitus (T2DM), 80 % of whom live in low- and middle-income countries (LMICs) [1]. Diabetic foot neuropathy (DFN) is a frequent complication and has enormous impacts on patients, families, and society. According to information from the US, 60–70 % of people with diabetes will develop peripheral neuropathy [2] and, of those, up to 25 % will develop a foot ulcer (DFU), a significant prognostic factor for future foot amputation [3].

While data from Peru is limited, our preliminary study found a 57 % prevalence of DFN at a National Public Hospital, 20 % of whom are considered to be high-risk for developing a DFU due to the presence of deformities [4]. In addition, the economic burden associated with DFUs – a mostly preventable condition – is enormous. Some projections indicate that the cost of treating one case of DFU with surgical debridement ranged between US$1,022 and US$1,404 in Peru, which is 200 % of the average monthly family income in Lima, Peru [5]. To avoid these preventative and costly complications, necessary strategies including patient education, foot care, and the promotion of appropriate footwear are needed.

Tools to identify early signs of foot damage or inflammation have the potential to reduce the incidence of foot ulceration and amputation. Thermometry, for example, measures superficial skin warmth and is a promising emerging modality to evaluate and manage early signs and help to prevent DFUs. In three independent clinical trials, Lavery and Armstrong found that utilization of thermometry among individuals with diabetes at high-risk of developing a DFU reduced rates of recurring ulcers four- to ten-fold [6–8]. Moreover, a systematic review indicated that the use of temperature monitoring is an effective way to predict and prevent diabetic foot ulceration [9].

Recently, a novel self-assessment device, TempStat™ (Visual Footcare Technologies, LLC, South Salem, NY, USA), a plastic panel with two polycarbonate plastic pads, has become available. The plastic pads are constructed of liquid crystalline cholesteric esters that react to skin surface temperature and change color to reflect temperature [10]. Frykberg et al*.* showed that TempStat™ can detect “alarm signs,” represented by a yellow color change, and the results positively correlate to temperature findings of infrared thermometer, the “gold standard” of thermometry devices [11]. As such, the use of TempStat™ is a low-cost, at-home, and patient-friendly way to prevent the development of DFUs and other complications such as amputation. The caveat for any thermometry device, however, is that the patient is required to adhere to self-assessment to achieve the observed efficacy; i.e., published results suggest that participants needed to evaluate their foot temperature on at least 50 % of the days to reduce the risk of foot ulceration [7].

In Peru and many other LMICs, clinical consultations are very short, lasting on average 10 − 15 minutes, which minimizes the time allowed for patient education [12, 13]. In addition, there are significant barriers in physician-patient communication [14], and medical treatment adherence is complicated by poor patient literacy and low socioeconomic status [15, 16]. The lack of resources for specialized diabetic follow-up programs leaves patients without knowledge of their disease process and unable to engage in self-care decision-making. Because of these problems, we need to identify ways to facilitate improved patient education and self-management for prevention of diabetic complications.

mHealth – the use of mobile technology to promote wellness – can close the gap between patient behaviors and the healthcare system. The use of Short Message Service (SMS) for diabetes management was evaluated by two systematic reviews, noting that patients with T2DM who received text message interventions showed improvements in Self-Efficacy for Diabetes and Diabetes Social Support Interview scores [17], and thus could improve clinically diabetes-related health outcomes [18].

Thermometry and SMS have independently demonstrated enormous potential to lead to positive diabetes-related outcomes in high-income countries. To strengthen these approaches in a LMIC in South America, we propose to use both modalities to evaluate the efficacy of a combination of foot thermometry with mHealth reminders, using SMS and voice messaging, in reducing the risk of foot ulceration in Peru.

## Methods/design

### Objectives

The main objective of this study is to compare the 1-year incidence of DFU in two arms: the intervention arm, receiving thermometry and mHealth reminders; and the control arm receiving thermometry alone. Our hypothesis is that subjects receiving SMS and voice messaging reminders will have a lower incidence of DFU than subjects who do not receive reminders. Additionally, we will compare patient compliance with thermometer use in both arms with a temperature-recording logbook.

#### Primary specific aim

Compare the incidence of DFU during the study period between those who receive thermometry alone and those who receive thermometry plus SMS and voice messaging

#### Secondary specific aims

Compare the compliance of foot thermometer use between the two study armsCompare the frequency of alarm signs reported to the study nurse between the two study armsCompare the frequency of alarm signs reported in the patient’s temperature-recording logbooks between the two study armsCompare the incidence of DFU according to pre-specified sub-groups: caregiving status, use of insoles and/or orthopedic shoesIn the intervention-only arm, compare the incidence of DFU by recipient of the messaging intervention (patient versus caregivers)

### Study design

This is a physician- and evaluator-blinded, 1-year, randomized clinical trial with two parallel groups, and a 1:1 allocation.

### Participant recruitment and selection criteria

Recruitment will be performed in the outpatient clinics of the aforementioned hospitals. Subjects will be eligible if they have a diagnosis of T2DM, are between 18 and 80 years of age, are in risk group 2 or 3 using the diabetic foot risk classification system (as specified by the International Working Group on the Diabetic Foot) [19–21], have a present dorsalis pedis pulse in both feet, have an operating cell phone or a caregiver with an operating cell phone, and have the ability to provide informed consent. Subjects will not be eligible for enrollment if they have current foot ulcers, active Charcot osteoarthropathy, severe peripheral arterial disease, or foot infection (Fig. 1).

**Fig. 1 Fig1:**
[figure not shown]
Process of screening evaluation. Legend: description of the inclusion and exclusion criteria of the study and screening process. IWGDF: International Working Group on the Diabetic Foot

Foot evaluation to place subjects into an eligible risk group will be performed using the diabetic foot risk classification system [22] as shown in Fig. 1. This evaluation includes a short questionnaire about previous history of ulceration and/or partial foot amputation, foot evaluation to detect deformities such as hallux valgus, rigid toe contractures (such as hammer or claw toes), and prominent metatarsal heads [19], and neuropathy testing using the vibration perception threshold and the Semmes-Weinstein monofilament (SWF) [22].

### Baseline data collection

We will record participants’ baseline data through questionnaires during visit 1, 1 week after enrollment (see Fig. 2). This information will include: (1) demographic evaluation, (2) socioeconomic evaluation, (3) lifestyles including tobacco, physical activity, and alcohol consumption, (4) mental health, specifically depression, (5) participants’ history of cardiovascular disease and diabetes, (6) current pharmacological treatment for diabetes, (7) pattern of use of insoles and orthopedic shoes, (8) mobile phone literacy, (9) anthropometric evaluation, and (10) blood pressure evaluation.

**Fig. 2 Fig2:**
[figure not shown]
Flow chart. Legend: description of the trial. HbA1c: Glycated Hemoglobin SMS: Short Message Service

Blood samples, to determine baseline levels of glycated hemoglobin, will be conducted at baseline, and at 6-month and at 12-month follow-up visits.

### Randomization

We will follow the Consolidated Standards of Reporting Trials (CONSORT) Statement of recommendations for the reporting of randomized trials [23]. Stratification and blocking randomization, using hospital site as a single strata, will be performed to generate a random allocation sequence. Stratification by recruiting hospital site will be used to ensure that the numbers of participants are closely balanced within intervention arms.

Subjects will be randomized to one of the two intervention arms via opaque, sealed envelopes, each bearing on the outside only the name of the hospital and a code. The preparation of envelopes will be perform using an independent researcher. Physicians providing care to study participants in recruiting sites will be blinded to the study arm allocation, and randomization will occur between 1 and 6 days after baseline data collection.

Study nurses will assign study codes to each of the study participants and, independently, codes will have been randomly assigned into the intervention arm or the control group. The study coordinator will be responsible for opening the sealed envelopes and informing participants about their assigned study arm as per the random list, as well as maintaining concealment. The subjects will be instructed not to discuss their treatment group assignment with the blinded evaluator.

### Intervention

As with any other complex intervention, we have used the recently proposed TIDieR –template for intervention description and replication checklist and guide – recommendations to describe our intervention [24]. Briefly, all study participants will receive education about foot care at the beginning of the study and they will all be provided with a thermometry device (TempStat™, Visual Footcare Technologies, LLC, South Salem, NY, USA). Participants in the intervention arm will receive, in addition to thermometry, an mHealth component as reminders in the form of SMS and voice messages.

#### Physical and informational materials

Videos were the chosen mechanism to standardize the education about foot care at the beginning of the study, and also to standardize the information about use of the TempStat™. In order to develop the content of our information materials, a communicator initially prepared a questionnaire to assess preferences about education on healthy habits through audiovisual media and to assess preferences related to video format. This was accomplished through a small pilot study conducted in diabetes outpatient clinics, with 30 volunteers, over a 2-week-long period. In parallel, a literature search was conducted to gather information to explain the etiology and risk factors for the development of neuropathy and ulcers, as well as to obtain recommendations for foot care practices and early signs of ulceration. After these procedures, three guides were prepared, two focused on foot care and one guide was oriented to provide instructions on the use of the TempStat™ device. Each of the guides was then used to generate three videos, all of them produced by an audiovisual specialist. All videos were validated by physicians and patients with T2DM. The two videos about foot care are available at https://youtu.be/qZm2z5Wbwg0 and https://youtu.be/3o0CkEmWeXk, and the one on how to use the TempStat™ device is available at https://youtu.be/KotgANRXoIw.

In addition to the videos, all study participants will be provided with a TempStat™ foot thermometer device. They will be instructed to use the device daily and will be asked to record their measurements in a temperature-recording logbook to be provided by the study nurse.

Finally, on the mHealth intervention arm only, SMS and voice messages will be sent to participants. The design and development process of these messages are provided as Additional file 1.

#### Procedures, activities, and processes

##### Enrollment visit

After screening, informed consent will be obtained from all participants by the study’s nurse; patients will be enrolled and a video about foot care will be shown to each participant. All of these procedures occur at the same visit, also known as the pre-screening and enrollment visit. The two videos about foot care will be shown to participants during enrollment (see Fig. 2).

##### Visit 1

One week after enrollment (see Fig. 2), the TempStat™ will be provided to each participant together with a video about its use. Participants’ usage of the TempStat™ will be observed by a study nurse to verify that they use it adequately. Some alarm signs have been pre-defined on the TempStat™ and the study nurse will train participants to detect them. These include: (1) yellow spots in any area of any feet for two consecutive days, (2) different colors in contralateral areas of the feet for two consecutive days, or (3) a dermal lesion. In any of these three scenarios, subjects will be instructed to contact the study nurse by phone or SMS. For the first two types of alarm signs, the contact nurse will ask about the presence of any lesions as well as the patient’s activity in the last 2 weeks. The nurse will also provide recommendations on how to decrease activity until temperatures normalize. If alarm signs continue for more than 1 week after the telephone consultation, a face-to-face evaluation will be requested to assess the patient for infection and/or a masked injury. If a dermal lesion is present, participants will be asked to be evaluated promptly by a nurse blind to the intervention. When a DFU, the main outcome, has been confirmed, the study nurse will direct the patients to receive professional specialty care.

##### Intervention arm

In the intervention arm, which includes an mHealth component, participants will receive two reminder messages and six foot-care promotion messages during the study period. The content of these eight messages has been developed and validated through both via SMS and voice messaging (see Additional file 1). During the first 2 weeks of the intervention, daily reminders to use the TempStat™ will be sent Monday to Friday via both SMS and voice messaging. Thereafter, for the remaining 50 weeks, patients will only receive two messages per week: one SMS and one voice message with the content alternating between reminders to use the TempStat™ device and promotion of foot care.

#### Intervention provider

Each participating site will have two study nurses and one study coordinator.

Nurses will have between 1 and 5 years of previous experience in diabetes care and will receive, as part of this study, a specific 2-day training in foot care, foot evaluation – vibration perception threshold (VPT), SWF, and pulse evaluation – as well as a description of the study procedures.

The study coordinator, an early career physician, will act as study coordinator and will provide support during the recruitment process. Study coordinators will have experience in epidemiological tools and research, and will be trained in detail in all study procedures.

#### Modes of delivery of the intervention

Recruitment of participants will be face-to-face. General education about foot care and the use of the TempStat™ will be delivered by audiovisual methods as previously described. Participants, under the observation of the study nurse, will perform a sample exercise using the TempStat™. After this, participants will then be asked to repeat the measurements every day at home and to record their observations in a temperature-recording logbook.

For the mHealth component, SMS and voice messages will be delivered to the participant’s or caregiver’s cell phones through an automated software system. Every week the system will be evaluated by the study coordinator to verify its functionality. More information about the software is available in Additional file 2.

#### Type of locations

Much of the intervention is about self-management of foot care in diabetes and occurs at home. Yet, the recruitment and enrollment into the study will be conducted at two third-level hospitals located in Lima, the capital of Peru: Hospital Nacional Cayetano Heredia and Hospital Nacional Arzobispo Loayza. Each hospital recorded over 50,000 outpatient visits of patients with diabetes in 2011 [25]. Both hospitals provide care for subjects of low socioeconomic status, much of the hospital care is subsidized through a national healthcare insurance but out-of-pocket payments for laboratory services and medicines are still very significant for this population [26]. Activities related to this protocol began in late September 2015 and are expected to continue through 2017.

#### When and how much?

After enrollment, participants will visit the clinic 1 week later to receive the TempStat™ device and instructions to use it. From that point, participants will visit the clinic every 2 months until the 12-month visit as shown in Fig. 2.

For the mHealth, during the first 2 weeks into study, the intervention arm will receive daily reminders to use the TempStat™ via both SMS and voice messaging. Thereafter, for the remaining 50 weeks, patients will only receive two messages per week: one SMS and one voice message, with content alternating between reminders to use TempStat™ and promotion of foot care. All messages will be delivered at 8 a.m.

#### Tailoring

Some form of tailoring occurs at the mHealth intervention arm. All the SMS will include the name of the participant (“Dear *participant’s name*, …) on, but not in, the voice messages. A minimal element of additional tailoring is anticipated to occur with all study participants, both intervention and control arms, during their face-to-face interactions with the study nurse, who will encourage them to perform daily home evaluations at the week 1 and each of the 2-month visits.

The thermometry intervention will be the same to all study participants and has been adapted from previous experiences in thermometry use [6–8]. The intervention has been designed to enhance self-care through a thermometry device to be used by participants themselves or with help from their caregiver. Each patient will be instructed at the beginning of the study about foot care and how to perform the thermometry following a standardized procedure demonstrated on videos.

#### Assessment of intervention adherence and fidelity

We plan to perform a process evaluation to evaluate fidelity of the intervention. The objective of this evaluation will be to: (1) determine if participants know how to use the TempStat™, (2) determine if participants receive SMS and voice messages, (3) determine if participants understand the messages, and (4) obtain opinions from the participants about feedback received from the nurse when they call because of an alarm sign. In addition, we will interview study nurses to collect their impressions about difficulties and limitations during the study period [27].

### Periodic assessments

Participants will be encouraged to maintain regular visits with their treating physician in the outpatient clinic. Each hospital will follow their standard of care for diabetes management without restrictions. Also participants will be asked to visit the diabetes clinic every 2 months for a general checkup and lower extremity evaluation by a nurse evaluator. If the nurse identifies an ulcer or any diabetic complication in a patient, the patient will receive conventional hospital treatment. At each 2-month visit, participants will: (1) complete a questionnaire about diabetes treatment, caregiver presence, and use of insoles and/or orthopedic shoes, and (2) have their weight and blood pressure measured. Glycated hemoglobin (HbA1c) will be measured at 6 and 12 months. In addition, information from participants’ temperature-recording logbooks will be recorded.

### Outcome measures

#### Primary outcome measure

The primary outcome is foot ulceration occurring at any point during the 12-month study period after randomization. Using the American Diabetes Association criteria [28, 29], foot ulceration will be defined as any break in the cutaneous barrier that usually extends through the full thickness of the dermis. The evaluator, blind to the intervention allocation, will be a trained nurse.

There will be two ways of identifying if a patient has developed foot ulceration: (1) during the bimonthly clinical nurse evaluations, and (2) if an alarm sign has been noted and prompted the participant to seek clinical evaluation (see Table 1).

**Table 1 Tab1:** Primary and secondary outcomes

Outcomes	Source of data	
	measure	End-point
Ulceration	Clinical evaluation by a trained nurse Participant’s report	Every 2 months until 12 months Any time during the 12 months
Adherence to daily temperature measurement	Logbook	Every 2 months until 12 months
Report of an alarm sign to the nurse	Nurse report	Every 2 months until 12 months
Report of an alarm sign in the logbook	Logbook	Every 2 months until 12 months
Dose-response analysis of SMS and voice messages	Automated system	Every 2 months until 12 months
Glycated hemoglobin	Blood sample	At 6 and 12 months
Sub-group analyses, in all participants		
Caregiving status	Participant’s report	Every 2 months until 12 months
Use of insoles and/or orthopedic shoes	Participant’s report	Every 2 months until 12 months
Sub-group analyses, intervention arm only		
Type of recipient (patient versus caregivers)	Participant’s report	Every 2 months until 12 months

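### Taking the message recipient from participant report every 2 months, in the messaging arm only, opens a possible unblinding route to the nurse who scores the primary outcome

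*Protocol article*

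**What the plan says.** All references are to the protocol article.

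- **The item.** In Table 1, under "Sub-group analyses, intervention arm only", stands "Type of recipient (patient versus caregivers"). Its source is participant's report and its timing is every 2 months until 12 months.
- **Who has a recipient.** Physical and informational materials: "on the mHealth intervention arm only, SMS and voice messages will be sent to participants".
- **The 2-month visit.** Under Periodic assessments, participants are asked to "visit the diabetes clinic every 2 months for a general checkup and lower extremity evaluation by a nurse evaluator". At each such visit they "complete a questionnaire about diabetes treatment, caregiver presence, and use of insoles and/or orthopedic shoes". No administrator of the questionnaire is named.
- **The blinding.** Primary outcome measure: "The evaluator, blind to the intervention allocation, will be a trained nurse". Randomization: "The subjects will be instructed not to discuss their treatment group assignment with the blinded evaluator".
- **Who knows the allocation.** Randomization: "The study coordinator will be responsible for opening the sealed envelopes and informing participants about their assigned study arm".
- **The messaging system.** Under Modes of delivery of the intervention, automated software sends messages to the phone of the participant or the caregiver, and the coordinator checks the system weekly.

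**The concern.** Participants know their arm, so the blinding of the nurse evaluator is the main protection for the primary outcome. That outcome leaves some room for judgment: the definition describes a skin break that usually, not always, goes through the whole dermis.

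The recipient of the messages exists in one arm only. A participant who says that the messages go to a daughter's phone, or to their own, has disclosed the allocation. The article tells participants to keep their assignment from the evaluator. Table 1 then has them report, on the evaluator's own 2-month cycle, something that reveals it. If the answer reaches the evaluator, later examinations of that participant are no longer blinded, and doubtful lesions could be scored differently by arm.

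**Working it through.** **1. Does the item identify the arm?** Yes. Messages go to the intervention arm only, and Table 1 confines the item to that arm. The neighbouring question on caregiver presence is put to both arms and reveals nothing.

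**2. Is it collected at the evaluator's visit?** Timing alone does not settle this. Table 1 gives the same 2-month timing to message dose (from the automated system) and to alarm signs reported to the nurse (from nurse report), and neither is a question put at a foot examination. Source and timing together are more informative:

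| Table 1 row | Source | Timing | In the visit questionnaire (Periodic assessments)? |
|---|---|---|---|
| Caregiving status | Participant's report | Every 2 months | Yes |
| Insoles/orthopedic shoes | Participant's report | Every 2 months | Yes |
| Type of recipient | Participant's report | Every 2 months | Not listed |

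The article describes no other 2-monthly occasion for participant report. Collection at the visit is thus the natural reading, but still an inference.

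**3. Does the evaluator hear or see it?** The documents do not say. Each site has two study nurses and one coordinator (Intervention provider), so someone else could collect it. Equally, both nurses receive the same foot-evaluation training, and nothing assigns this item to a person other than the evaluator.

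**4. How many examinations could be exposed?** Visits every 2 months to month 12 give 12 / 2 = 6 scheduled examinations. If the item is heard before the month-2 examination, 6 of 6 are exposed. If it is first heard after that examination, 6 − 1 = 5 of 6 are. Both are upper bounds that apply only if the evaluator is exposed to the item.

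**5. What could exposure do?** No figure in the documents answers this, so the following is an illustration on assumed inputs. It uses the planned 78 per arm, which I reproduced first. With 30% vs 8.5%, two-sided alpha 0.05 and power 0.9 (the article does not state sidedness):

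- Mean proportion = (0.30 + 0.085)/2 = 0.1925; difference = 0.215.
- n = [1.960·√(2·0.1925·0.8075) + 1.2816·√(0.30·0.70 + 0.085·0.915)]² / 0.215² = 68.6, so 69.
- With continuity correction: (68.6/4)·[1 + √(1 + 4/(68.6·0.215))]² = 77.6, so 78, as stated.

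Now assume a true ulcer rate of 30% in both arms, and that a share m of all intervention-arm ulcers is never scored as an ulcer. The observed intervention rate is 0.30·(1 − m). For m = 0.20:

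- Observed rate = 0.24; difference = 0.06; mean = 0.27.
- SE under the null = √(2·0.27·0.73/78) = 0.0711; SE under the alternative = √((0.21 + 0.1824)/78) = 0.0709.
- P(reject, favouring intervention) = Φ((0.06 − 1.960·0.0711)/0.0709) = 0.132.
- P(reject, other direction) = 0.0025. Total = 0.134.

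| Assumed missed share m | Observed rate, intervention | Two-sided rejection rate |
|---|---|---|
| 0 | 30% | 5.0% |
| 5% | 28.5% | 5.5% |
| 10% | 27% | 7.0% |
| 20% | 24% | 13.4% |
| 30% | 21% | 25.1% |

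This is a normal approximation that leaves out the site term of the planned model. It takes m as a share of all ulcers, not only of doubtful ones. An ulcer passed over once may be scored at a later visit, which would make m smaller.

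**The case against.** The strongest reply is that the decisive step is not in the documents. The visit questionnaire as listed omits the message recipient. A participant's report says who supplies the information, not who receives it. The coordinator, who is unblinded and checks the messaging system weekly, could collect it, and the section on Visit 1 distinguishes a contact nurse from a nurse blind to the intervention. Who administers which form is operational detail that an article may leave to its data-collection manuals.

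Most of this stands. A reader might infer that the plan has the blinded nurse ask the question, or that Table 1 contradicts the instruction under Randomization. Neither follows: both passages can be obeyed if someone else collects the item. Nor is silence about the form's administrator a finding.

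What remains is the source that the article does state. Table 1 fixes participant report on the evaluator's schedule for an item that discloses the arm, although the same table already takes message dose from the automated system.

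A further objection is that repeated reporting may serve a purpose, because the recipient can change over 12 months and the article does not say that the system stores whose phone it is. That is fair, and any replacement source has to provide for it.

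**Conclusion.** The point holds as a possible unblinding route for the primary-outcome assessor, created by a stated data source and worth closing. It is not evidence that blinding is broken.

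It rests on two facts in the article (the item exists in one arm only; it is participant-reported every 2 months) and one inference (that it is collected at the 2-month visit, like the two rows with the same source and timing). Exposure of 5 or 6 of the 6 scheduled examinations is a ceiling, conditional on the evaluator hearing or seeing the answer.

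A reader might also take the rejection rates above as the expected bias. They are not: the missed share and its direction are assumed, and the documents support no particular value. They show only that a small missed share does little harm and that a share of 20% to 30% would matter.

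**What to change.** In Table 1, change the source for type of recipient from participant's report to the messaging-system registration kept by the study coordinator. The coordinator records at set-up, after randomization, whether the registered phone is the patient's or a caregiver's, and updates the entry if it changes.

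State that this item is kept off the evaluator's forms and is not raised in the evaluator's presence. Apply the same rule to the process-evaluation questions on receiving and understanding messages (Assessment of intervention adherence and fidelity), which disclose the arm in the same way.

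The cost is small: one changed table entry, one sentence, and a patient/caregiver label for the coordinator to record and maintain. No extra staff or visits are needed, and the sample size, the primary analysis and the sub-group comparison itself are unchanged.
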